## Methods and analysis

### Study design

A quasi-experimental mixed-methods approach will be used to determine the feasibility and acceptability of implementing online volunteer-led exercise sessions in community clubs. The study will be conducted at community-clubs focused on promoting social interaction among older people. Feasibility studies are used to determine whether an intervention is appropriate for further evaluation, to determine sample sizes for controlled trials and to assess whether the ideas and findings can be shaped to be relevant and sustainable. In this study, the feasibility of training volunteers to promote increased physical activity among community-dwelling older adults will be assessed. The acceptability of the intervention will be examined through qualitative interviews to explore the views and experiences of volunteers, older adults participating in the study, and their carers or family members. The impact of the intervention on physical activity levels and functional outcomes will also be measured. This will help inform the sample size calculation for a future effectiveness trial.

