### Participant recruitment

#### Volunteer recruitment

The research team will be invited by club staff to attend the virtual clubs to introduce the study. Club volunteers and members who are interested in leading the group exercise will indicate their interest to staff members or approach the research team directly. To lead the group exercise, volunteers must be physically able to perform the exercises themselves and be able to provide written consent. This will be assessed at the training sessions by the trainer (SM).

The participant information sheet and the consent form will be sent through the post. Club members are invited to contact the research team for further discussions about the study. Once the research team has received the signed consent form, volunteers will be invited to participate in the online training. To deliver online group exercise to 30 exercise participants, it is estimated that at least 12 volunteers will be needed to lead 6 online groups. Volunteers will be paired up to lead and deliver the intervention.

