### Data analysis plan

#### Quantitative data analysis

Data collected will be double entered into a secured database for analysis. Statistical analysis will be conducted using the statistical software SPSS Statistics V.25. Descriptive statistics—median (IQR); mean (SD); number (%)—will be used to analyse the numbers of volunteers recruited, trained, and retained, as well as the type and extent of progression of the seated exercise, and duration of their activity, and patients’ adherence to the intervention. Analysis of the above outcome measures will be used to develop an assessment of the feasibility of delivering this intervention. Adherence to the intervention and reasons for non-adherence will be reported.

Outcome measures recorded at baseline will be compared with measurement at 6 months to determine if the PA intervention had an impact on physical activity levels measured by CHAMPS, functional outcomes including performance in ADLs (Barthel Index), quality of life (EQ-5D-5L), frailty status (PRISMA-7) and sarcopenia status (SARC-F). The distribution of each outcome measure will be assessed for normality. Depending on the skew of the data, parametric (t-test) or non-parametric (Mann-Whitney U test) statistics will be used for continuous variables. χ^2^ test will be used for categorical variables.

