#### Strengths and limitations of the study

This study explores a novel approach of training volunteers to deliver online group exercise to older adults. Application of a mixed-methods approach in this study will help determine the feasibility of the intervention and explore barriers and facilitators to a successful implementation of the intervention. However, a limitation of the study is the lack of a control group. Recruitment of older adults will be through established social clubs, in which recruiting some older adults and excluding others from participating in the exercise groups would be a challenge. Additionally, as this is a feasibility study, we will use a range of social clubs of varying sizes, and client groups with different age ranges and physical abilities, to explore different approaches to the intervention rather than including a control group. Nevertheless, this study has been designed to assess the feasibility and acceptability of the intervention with a view to informing the development of a toolkit to support the wider implementation of the intervention and a future controlled experimental design. This study excluded older adults who are not able to walk. Patients who are bed-bound will not be able to participate in the seated exercises without additional support. This additional support cannot be met by this study. As the intervention is delivered remotely, participants must have a level of independence to participate safely. Additionally, one of the key outcome measure is physical activity levels and older adults who are bed-bound will have minimal activity levels.

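### The tests named for the baseline-to-6-month comparison give wrong error bars: they do not secure pairing within person, and none allows for delivery in about six volunteer-led groups

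*Protocol article*

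**What the plan says.** The Quantitative data analysis section sets a within-person comparison: "Outcome measures recorded at baseline will be compared with measurement at 6 months to determine if the PA intervention had an impact". The outcomes are CHAMPS, the Barthel Index, EQ-5D-5L, PRISMA-7 and SARC-F. For continuous outcomes the section states: "Depending on the skew of the data, parametric (t-test) or non-parametric (Mann-Whitney U test) statistics will be used for continuous variables". For categorical outcomes, a chi-squared "test will be used for categorical variables". There is no comparison arm; the Strengths and limitations section says that "a limitation of the study is the lack of a control group".

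The Volunteer recruitment section fixes how the intervention is delivered: "To deliver online group exercise to 30 exercise participants, it is estimated that at least 12 volunteers will be needed to lead 6 online groups", and "Volunteers will be paired up to lead and deliver the intervention". The analysis section has no term for online group or club and does not mention clustering.

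On later use of the results, the Study design section says of the measured impact: "This will help inform the sample size calculation for a future effectiveness trial".

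**The concern.** Two features of the data are missing from the named tests, and they pull in opposite directions.

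- **Pairing.** Each person is measured twice. Mann-Whitney U and chi-squared treat the two occasions as separate samples of people. Because Mann-Whitney U is given as the alternative to the t-test, the t-test may be meant as unpaired too. Ignoring a positive correlation between occasions overstates the standard error of the change.
- **Grouping.** People in one online group share leaders, sessions and often a club. The article itself expects groups to matter: it runs fidelity checks on volunteers' delivery, explores group dynamics in the interviews, and plans clubs that differ in size, age range and physical ability. If changes are alike within a group, treating 30 changes as independent understates the standard error.

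At stake are the intervals and p-values by which the study judges whether the intervention had an impact, and the variability figures passed on to a later sample size calculation. Someone who notices only the first fault and switches to a paired t-test would move from intervals that may be too wide to intervals that are too narrow.

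**Working it through.** **Inputs from the protocol article.** 30 participants, 6 groups, 12 volunteers in pairs. The plan's own arithmetic is consistent: 12 / 2 = 6 groups and 30 / 6 = 5 people per group. The target of 30 has no power calculation behind it to reproduce.

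**Inputs assumed.** The ICC of the change scores (0.02 to 0.20) and the baseline-to-6-month correlation r. The article gives neither.

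**Step 1: a paired test that ignores groups.** Design effect DE = 1 + (5 − 1) × ICC. True SE / naive SE = √DE. Effective n = 30 / DE. Type I error comes from simulating 6 groups of 5 with normal changes at a nominal two-sided 5%.

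| ICC | DE | True SE / naive SE | Effective n | Type I error |
|---|---|---|---|---|
| 0.02 | 1.08 | 1.04 | 27.8 | 5.8% |
| 0.05 | 1.20 | 1.10 | 25.0 | 7.2% |
| 0.10 | 1.40 | 1.18 | 21.4 | 9.6% |
| 0.20 | 1.80 | 1.34 | 16.7 | 14.3% |

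A t-test on the six group mean changes (5 df) stays at about 5% throughout.

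**Step 2: an unpaired test on the same data.** With equal variances σ² at the two times, the unpaired SE² is 2σ²/30. The true SE² of the mean change is 2σ²(1 − r)DE/30. The ratio of true to unpaired SE is therefore √((1 − r) × DE):

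| ICC | r = 0.1 | r = 0.3 | r = 0.5 | r = 0.7 |
|---|---|---|---|---|
| 0.02 | 0.99 | 0.87 | 0.73 | 0.57 |
| 0.05 | 1.04 | 0.92 | 0.77 | 0.60 |
| 0.10 | 1.12 | 0.99 | 0.84 | 0.65 |
| 0.20 | 1.27 | 1.12 | 0.95 | 0.73 |

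Below 1, the unpaired interval is too wide; above 1, too narrow. The two faults cancel at r = 1 − 1/DE, which is 0.07 / 0.17 / 0.29 / 0.44 for the four ICCs. Simulated type I error of the unpaired t-test at r = 0.5 is about 1% / 1% / 2% / 4%. At r = 0.7 it is at most about 1%. At r = 0.3 it is 3.2% / 4.7% / 8.2% for ICCs of 0.05 / 0.10 / 0.20.

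**Step 3: can this study supply an ICC?** With 6 groups of 5, F = (1 + 4 × ICC) / (1 − ICC) on 5 and 24 df gives an exact 95% interval. An estimate of 0.05 has an interval of −0.14 to 0.58; an estimate of 0.10 has −0.11 to 0.64. At an upper limit of 0.58 the design effect for groups of 5 would be 1 + 4 × 0.58 = 3.3. A point estimate is therefore of almost no use for sizing a trial.

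**Step 4: cost of allowing for group.** Simulated intervals from the six group means average 1.21 times the width of the paired interval that ignores groups at ICC 0, and 1.44 times at ICC 0.10.

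**The case against.** The strongest objection concerns direction. A reader might infer from the grouping alone that the planned error bars are too narrow. The article does not support that. The Step 1 figures belong to a paired test, and the analysis section does not say that one will be used. For the tests as written, Step 2 shows conservative results at a correlation of 0.5 or more over the whole ICC range considered. This objection stands, so the point is confined to error bars that are wrong, with a direction that depends on how the t-test is run and on two unknown correlations.

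A reader might also infer that the future trial will be underpowered because no ICC is produced here. That does not follow either. The article says only that the results will help inform the sample size. It does not say that the later trial will be delivered in groups, or that participant-level SDs alone will be used. Six groups could not estimate an ICC usefully in any case.

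Three further points stand in part.

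- Six groups is a planning estimate, and the article does not say that a group keeps the same leaders throughout. The size of the effect is therefore illustrative.
- If club matters as well as group, the six group means need not be independent. The interview targets (at least two participants per club, 10 in all; at least one volunteer per club, five in all) suggest no more than five clubs. The simulation included no club effect.
- A condensed article may leave model detail to a fuller document. But this article does name its tests, and two of the three do not fit paired data.

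**Conclusion.** The point holds in limited form, at minor severity. The named tests do not match the design in two respects: within-person pairing is not secured, and grouped delivery is ignored. Taken unpaired, they give intervals that are too wide once the baseline-to-6-month correlation exceeds about 0.07 to 0.44, depending on the ICC. With pairing corrected and grouping still ignored, the true SE would be about 4% to 34% larger than the one reported, and type I error about 6% to 14%, for ICCs of 0.02 to 0.20. Every size here rests on assumed ICCs and correlations, six equal groups of 5, and normal changes.

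Severity is minor because the primary outcome is feasibility, reported descriptively. The tested scores are secondary in an uncontrolled study, and the article ties no decision rule to their p-values.

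**What to change.** Replace the sentence on tests so that it says the following.

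- **Continuous outcomes:** analyse the within-person change from baseline to 6 months, and report the mean change with a 95% interval that allows for online group. Use either a random intercept for group with small-sample (Satterthwaite) df, or a t interval on the group mean changes with df equal to the number of groups minus 1 (5 df with six groups). List the group mean changes, and identify the club of each group so that shared clubs are visible.
- **Categorical status (frailty, sarcopenia):** use a paired method, such as McNemar's test for a binary status, in place of chi-squared.
- **Future sample size:** work over a stated range of ICCs and not from a point estimate. If an ICC is reported, give its interval and say that about six groups cannot estimate it usefully.

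The cost is a few sentences in the analysis section and a little extra work in the same software, with no new data. The downside is intervals about 1.2 times (ICC 0) to 1.4 times (ICC 0.10) as wide as those of a paired analysis that ignores groups.

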#### Qualitative data analysis

Data collected from the interviews will be transcribed verbatim and analysed with an inductive thematic analysis approach.^41^ This approach includes: phase 1—familiarising with the data, phase 2—generating initial codes, phase 3—searching for themes, phase 4—reviewing themes, phase 5—defining and naming themes and phase 6—producing the report. Analysis of qualitative data will be conducted using NVivo. A sample of transcribed text will be read and coded separately and then together by two researchers to create a coding manual that applies to the entire set of transcripts. The codes will be analysed to generate concepts and ideas to determine the acceptability of the intervention, and to identify facilitators and barriers to the implementation process. The codes act as tags or labels to help catalogue key concepts embedded within the raw data. From the codes, themes will be developed to reflect the views and experiences of the community-dwelling older adults and volunteers regarding the online physical activity intervention.

A toolkit that will support a wider implementation of the intervention will be developed. It will be a written manual which contains the training programme, exercises, competency checklists and information on how best to implement the intervention, taking into consideration the barriers and facilitators determined through the qualitative interviews.

### Patient and public involvement

Patient and public involvement (PPI) involvement was sought in the development of this protocol. Visits were made to two clubs and discussions were held among club volunteers and club attendees about this project. Their views on what type of activities and the frequency of the activities were explored. Club attendees were also asked about what outcomes were important to them, which will be included in the study.

SA who is a coapplicant in this study, will also represent the views of club members and volunteers. She is the head of clubs for the organisation and is experienced in coordinating clubs. She has an overview on how the clubs are conducted and her input on the practical aspects of implementing the intervention will be invaluable. Her practical experience gained through interaction with club members and volunteers will help ensure that their views are represented.

Two additional PPI representatives will be invited to be part of the study management group led by the PPI lead for the Ageing and Dementia theme within the Wessex Applied Research Collaboration (ARC). This group will aim to meet up quarterly to discuss the study progress and will be involved in the design of the research, discussion of the results and dissemination of research findings. PPI has also been involved in the preparation of public-facing materials and study documents.

#### Strengths and limitations of the study

This study explores a novel approach of training volunteers to deliver online group exercise to older adults. Application of a mixed-methods approach in this study will help determine the feasibility of the intervention and explore barriers and facilitators to a successful implementation of the intervention. However, a limitation of the study is the lack of a control group. Recruitment of older adults will be through established social clubs, in which recruiting some older adults and excluding others from participating in the exercise groups would be a challenge. Additionally, as this is a feasibility study, we will use a range of social clubs of varying sizes, and client groups with different age ranges and physical abilities, to explore different approaches to the intervention rather than including a control group. Nevertheless, this study has been designed to assess the feasibility and acceptability of the intervention with a view to informing the development of a toolkit to support the wider implementation of the intervention and a future controlled experimental design. This study excluded older adults who are not able to walk. Patients who are bed-bound will not be able to participate in the seated exercises without additional support. This additional support cannot be met by this study. As the intervention is delivered remotely, participants must have a level of independence to participate safely. Additionally, one of the key outcome measure is physical activity levels and older adults who are bed-bound will have minimal activity levels.

### Ethics and dissemination

#### Ethical and safety considerations

This study has received ethical approval from the University of Southampton Faculty of Medicine Ethics Committee and Research Integrity and Governance committee (ID: 52 967.A1). Data will be stored on university repository PURE and will be made available to other researchers on request.

#### Dissemination plan

Findings from this study will be published in peer-reviewed journals and presented at national and international scientific platforms. A toolkit will be developed to support future implementation plans.
